### Study objectives

The primary objective is to compare the short-term appetite of patients who undergo MIPG for gastric and gastroesophageal adenocarcinoma with that of patients who undergo MITG. We hypothesize that MIPG is associated with higher postoperative appetite levels compared with MITG, which would result in better nutritional status and less body weight loss after surgery.

The secondary objective is to assess PROs and nutrition measures and compare them between the MIPG and MITG groups. We will use the MD Anderson Symptom Inventory Gastrointestinal Cancer Module (MDASI-GI) questionnaire, along with an additional three experimental question items (MDASI-GI +), to collect preoperative and postoperative PRO measures of QoL, and we will check fasting ghrelin levels to correlate them with reported appetite levels. We will also investigate factors associated with improved QoL after surgery, safety of MIPG and MITG, and oncologic outcomes after MIPG and MITG.

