## Methods/design

This is a multicenter, open-label, prospective cohort study comparing outcomes of MIPG (trial procedure) and MITG (standard of care, control group). We expect to enroll a total of 60 patients in this study (30 per group). Patients will be recruited from and treated at MD Anderson Cancer Center, Mayo Clinic, Memorial Sloan Kettering Cancer Center, Yonsei University, and Keio University, after Institutional Review Board approval for each institution. We plan to enroll at least 20 patients each from Asian (Keio University and Yonsei University) and US (MD Anderson, and Mayo Clinic Minnesota, and Memorial Sloan Kettering Cancer Center) institutions. The total study duration is expected to be 60 months (including enrollment and follow-up). We will prospectively collect PROs longitudinally for a 1-year period. Other clinical factors will also be collected to investigate factors associated with improved PROs.

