#### Nutritional measures

Body weight and serum levels of albumin, ferritin, vitamin B_12_, hemoglobin, and ghrelin will be measured at baseline and 1, 3, 6, and 12 months after surgery.

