### Statistical methods

The primary outcome is appetite level score (with 0 being the best and 10 being the worst) according to the MDASI-GI + (Question #8) at 3 months after surgery. We will enroll a total of 64 patients in order to have 60 evaluable patients at 3 months after surgery (i.e., assuming a 5% attrition rate). With 30 patients expected in each cohort, this study will have 80% power to detect a one-point difference in appetite level score using a two-sample *t*-test with a 5% significance level and assuming a common standard deviation of 1.35 (nQuery Advisor 7.0). We will also compare serum ghrelin levels at 3 months after surgery. For the primary analyses, we will apply the inverse probability treatment weights using propensity scores for assessing the difference between the two surgical groups. Inverse probability weighting is applied by weighting the outcome measures by the inverse of the probability of an individual with a given set of covariates being assigned to their treatment (i.e., propensity score). The propensity scores will be derived through fitting a multiple logistic regression model with MIPG (vs. MITG) as the outcome variable. Then, in the presence of measured confounders, we can estimate the difference between the two treatment groups via inverse probability weighting of the study subjects. For the regression analyses described below for assessing the “surgical procedure” effect, the inverse probability treatment weights using propensity scores will be applied as appropriate in addition to any standard statistical methods. The two-sample t-test or Wilcoxon rank-sum test will also be used to compare the appetite level or ghrelin level at 3 months, as well as the percent change from baseline, between the two cohorts. We will longitudinally collect PROs (using the fully translated MDASI-GI +) and compare specific items and overall scores as well as body weight, body mass index, and albumin and hemoglobin levels at 1, 3, 6, and 12 months after surgery in the cohorts. A linear mixed effects model will be fit to assess the change in QoL over time while accounting for potential intra-patient correlations. “Time” points will be included as a fixed effect, and “patient” will be included as a random effect. The surgical procedure received and use of adjuvant or neoadjuvant therapy will be included as covariates. Similar analyses will be performed to assess the changes in body weight, body mass index, and albumin and hemoglobin levels over time. The number of LNs examined pathologically, incidence of postoperative complications, operating room time, blood loss, and length of hospital stay will be compared. Continuous variables (such as length of hospital stay) will be assessed using the two-sample t-test or Wilcoxon rank-sum test. Categorical variables (such as type and severity of complications) will be assessed using Fisher’s exact test. Local–regional recurrence-free and overall survival will be estimated using the Kaplan–Meier method, and Cox regression analyses will be performed to assess the association with patient characteristics and surgical procedure received. The 3-year loco-regional recurrence rate will be estimated along with the 95% confidence interval. Missing data will be excluded from analysis and no missing data imputation will be performed. Sensitivity analyses to investigate factors associated with PRO scores, including but not limited to country (west vs. east), tumor location, types of reconstruction after PG, use of neoadjuvant and adjuvant therapy, use of jejunostomy or nutrition status, on PRO scores will be performed.

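### The plan predicts less weight loss after MIPG, but neither stated weight analysis clearly tests a difference in loss between the procedures

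*Protocol article*

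**What the plan says.** All references are to the protocol article.

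- **Hypothesis (Study objectives).** Higher appetite after MIPG is expected, "which would result in better nutritional status and less body weight loss after surgery". Loss is a change from the preoperative state.
- **Endpoint (Nutritional measures).** The section reads: "Body weight and serum levels of albumin, ferritin, vitamin B_12_, hemoglobin, and ghrelin will be measured at baseline and 1, 3, 6, and 12 months". Weight is listed as a value at each visit. Loss and percent loss are not defined.
- **Visit comparisons (Statistical methods).** The cohorts are to be compared on weight and BMI as measured: "compare specific items and overall scores as well as body weight, body mass index, and albumin and hemoglobin levels at 1, 3, 6, and 12" (visits in months).
- **Longitudinal model (Statistical methods).** For QoL, a linear mixed model has time as a fixed effect and patient as a random effect, and "The surgical procedure received and use of adjuvant or neoadjuvant therapy will be included as covariates". For weight: "Similar analyses will be performed to assess the changes in body weight, body mass index, and albumin and hemoglobin levels over time".
- **Where change from baseline is named as a cohort contrast.** Only for the primary variable and ghrelin: "compare the appetite level or ghrelin level at 3 months, as well as the percent change from baseline, between the two cohorts".
- **Setting.** Procedure is chosen by patient and surgeon (Details of surgery). Regional minimums apply to the whole cohort and not within procedure: "We plan to enroll at least 20 patients each from Asian (Keio University and Yonsei University) and US" institutions (Methods/design). Inverse probability weights are to be used in the regression analyses where appropriate.

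**The concern.** A patient's weight in kilograms at 3 or 12 months depends heavily on weight before surgery. A between-group comparison of that level mixes any difference in loss with any difference in starting weight. In this cohort, starting weight could differ between groups because allocation is not randomized and patients come from both the US and Asia. The Background describes PG as increasingly used in South Korea and Japan and TG as the Western standard, so regional imbalance by procedure is plausible, although the documents do not predict it.

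Two things are at stake for the weight endpoint. One is precision: variation in body size between patients can swamp the effect even when regions are balanced. The other is bias: a real weight-sparing effect of MIPG could be hidden, and in an extreme case could appear with the wrong sign.

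**Working it through.** **1. The plan's own figures.** The only power statement concerns appetite: 1 point, SD 1.35, 30 per group, 5% level, 80% power. An exact two-sided t-test gives 80.5%. Enrolment of 64 for 60 evaluable at 5% attrition also reproduces (60 / 0.95 = 63.2, rounded up to 64). Both are correct and do not bear on weight, for which the plan gives no figure.

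**2. What each planned contrast estimates.** Let B be mean baseline weight and L the fractional loss at a visit.

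- Visit comparison: B(MIPG)·(1 − L(MIPG)) − B(MITG)·(1 − L(MITG)). It contains the baseline difference.
- Mixed model with time + procedure: with complete visits, the procedure coefficient is the level difference averaged over the visits in the model. If baseline is one of them, a visit with no treatment effect is averaged in. The time effect describes change pooled over both groups.
- Percent-loss contrast: L(MITG) − L(MIPG), which is free of B.

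**3. Assumed inputs (none are in the documents).**

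- Set A: mean weight 85 kg (US) and 62 kg (Asia), within-region SD 14 kg, true benefit 3 percentage points, SD of percent loss 6 points.
- Set B: US mean 80 kg, regional gap 5 to 20 kg, loss 10% after MIPG and 15% after MITG. For power: SD of weight 10 to 15 kg, SD of percent loss 5 to 8 points.

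**4. Precision with regions balanced, 30 per group, two-sided 5% t-test.**

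- Set A: effect = 0.03 × 73.5 = 2.2 kg. Raw SD = √(14² + 23² × 0.25) = 18.1 kg. Standardized effect = 2.2 / 18.1 = 0.12, power about 7%. On percent loss, 3 / 6 = 0.5 SD, power 48%.
- Set B: 3.5 kg with SD 10 to 15 kg gives 27% down to 14%. Five points with SD 5 to 8 gives 97% down to 66%.

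**5. Bias with regions unbalanced: unweighted group means, MIPG minus MITG.**

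Set B, 15 kg gap:

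| Asian share, MIPG / MITG | Baseline means, kg | Absolute difference, kg | Difference in percent loss |
|---|---|---|---|
| 50 / 50 | 72.5 / 72.5 | 65.25 − 61.63 = +3.6 | 5 points |
| 60 / 40 | 71.0 / 74.0 | 63.9 − 62.9 = +1.0 | 5 points |
| 67 / 33 | 70.0 / 75.0 | 63.0 − 63.8 = −0.8 | 5 points |

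At 67/33, gaps of 5, 10, 15 and 20 kg give +2.4, +0.8, −0.8 and −2.3 kg.

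Set A, with its larger 23 kg gap: at 65/35 the baseline difference is 0.30 × 23 = 6.9 kg, so the net is about −6.9 + 2.2 = −4.7 kg. At 60/40 it is about −4.6 + 2.2 = −2.4 kg.

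**6. The mixed model.** Simulation under Set B: 100 runs, 60 patients, 15 kg gap, within-region SD 10 kg, SD of loss 5 points, baseline included as a time point, no weighting.

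| Contrast | 67/33: mean (runs negative) | 50/50: mean (runs negative) |
|---|---|---|
| Absolute difference at 12 months | −1.0 kg (58%) | +3.5 kg (11%) |
| Procedure coefficient, time + procedure | −2.5 kg (73%) | +2.2 kg (19%) |
| Procedure-by-time at 12 months | +4.4 kg (0%) | +3.7 kg (0%) |
| Percent change at 12 months | +5.2 points (0%) | +5.0 points (0%) |

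The mixed model as described therefore shares the weakness of the visit comparison. Both change contrasts keep the correct sign in every run.

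**The case against.** **Change in weight is planned.** This is the strongest point against the concern. The plan says it will model changes in weight and BMI over time, and baseline weight is collected. A reader could infer that absolute levels are the only comparison and that weight change is ignored; the text does not support that. What remains is narrower: the stated model terms do not deliver a between-procedure contrast in change.

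**Adjustment is planned.** Inverse probability weights are to be applied to the regression analyses as appropriate, and a propensity model containing region or baseline weight would reduce the bias. The unweighted figures above do not show what a weighted analysis would give. The propensity covariates are not listed, which an article may leave to the full protocol, so that is not counted as a fault. Weighting does not turn a level contrast into a contrast in loss.

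**The sizes are assumed.** A reader might also infer that the comparison mainly measures body size and region and will give the wrong sign. The documents give no weight SD, no regional gap and no procedure split by region. Under Set B the sign is right when regions are balanced, and also at 60/40 with a 15 kg gap. Reversal at 60/40 appears only with the 23 kg gap of Set A. Reversal is a possibility, not an expectation.

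**The endpoint is secondary, and model detail often sits in an analysis plan.** Both are true. However, the article does state the model terms, and it names percent change for other variables but not for weight. The mismatch is therefore in what is written.

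**Albumin and hemoglobin.** The body-size argument does not extend to serum concentrations. No error is shown for them.

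**Conclusion.** The concern holds in a limited form. The hypothesis is about weight loss. The visit comparisons use absolute weight and BMI, and the mixed model, as described, gives an average difference in level. Neither clearly tests a difference in loss.

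The loss of precision does not depend on regional imbalance: about 7% against 48% power under Set A, and 14–27% against 66–97% under Set B. A hidden benefit requires regional imbalance by procedure, or some other baseline weight difference, that the weights do not remove. A reversed sign further requires a large regional weight gap, combined in Set B with strong imbalance. All these sizes rest on assumed weights, SDs and effects. The primary appetite analysis is not affected.

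**What to change.** In Statistical methods, and to match in Nutritional measures, adopt one of the following:

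- Define the weight contrast as percent change in weight (and BMI) from the preoperative value at 1, 3, 6 and 12 months, compared between MIPG and MITG with the same propensity weights as the primary analysis.
- Or, in the planned mixed model, include baseline as a time point with a procedure-by-time interaction, or adjust post-baseline values for baseline, and report the procedure contrast at each visit.

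Percent change is the cleaner scale, because kilograms lost still depend somewhat on starting weight. Under Set B with a 15 kg gap, the expected contrast in kilograms lost is 10.9 − 7.25 = 3.6 when regions are balanced and 11.25 − 7.0 = 4.25 at 67/33, for the same 5-point effect.

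Show absolute weight and BMI descriptively. Baseline adjustment of albumin and hemoglobin is an optional gain in precision, not a correction.

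Cost: a wording change with no new data, since baseline weight is already planned. Patients without a recorded preoperative weight drop out of the percent-change analysis.

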#### Posttreatment outpatient evaluation

Post-discharge follow-up evaluations for PRO collection will occur at 1 month (± 2 weeks) and 3, 6, and 12 months (± 1 month) after surgery. These may be performed in person or by telephone, email, or website-based reporting system (REDCap), and data will be subsequently stored in the REDCap database, which will be managed at MD Anderson (center institution of this study).

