### Outcome measures

The primary endpoint is appetite level (reported on a 0–10 scale, in Q8 of MDASI-GI +) at 3 months after surgery. The individual and total MDASI-GI + scores will also be reported at baseline (preoperative) and 1, 3, 6, and 12 months after surgery.

The secondary endpoints below will be collected retrospectively from the medical record.

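### The secondary longitudinal model, read as a patient random intercept with independent residuals, assumes equal correlation between all visits, so standard errors for change over time are wrong if correlation varies with interval

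*Protocol article*

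**What the plan says.** All of this is in the protocol article.

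- **Purpose (Statistical methods):** "A linear mixed effects model will be fit to assess the change in QoL over time while accounting for potential intra-patient correlations".
- **Terms (Statistical methods):** the only random effect named is patient, which "will be included as a random effect". Time enters as a fixed effect by visit. On the other terms the article writes: "The surgical procedure received and use of adjuvant or neoadjuvant therapy will be included as covariates". No random slope, residual covariance or robust standard error is named. Independent residuals are not stated either, and no procedure-by-time term is listed.
- **Reach (Statistical methods):** similar analyses are planned for body weight, BMI, albumin and hemoglobin.
- **Visits (Outcome measures):** questionnaire scores "will also be reported at baseline (preoperative) and 1, 3, 6, and 12 months after surgery".
- **Windows (Posttreatment outpatient evaluation):** "1 month (± 2 weeks) and 3, 6, and 12 months (± 1 month) after surgery".

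The model is secondary. The primary analysis is the inverse-probability-weighted comparison of appetite at month 3.

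**The concern.** The article does say how within-patient correlation will be handled: through a patient random effect. In its ordinary sense that is a random intercept. With independent residuals of equal variance, it gives every pair of visits the same correlation, whether they are 2 or 11 months apart. The visits are unequally spaced and cover recovery and, for some patients, adjuvant therapy. If baseline is a response in the model, they also straddle the operation. Equal correlation over such a schedule is a strong assumption.

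The assumption bears directly on the model's declared purpose. The standard error of a change between two visits depends on the correlation of that particular pair. A model with one averaged correlation gives every change the same standard error, which is too small for some pairs and too large for others whenever the true correlations differ. At stake are the tests and confidence intervals for the one-year course of five kinds of outcome.

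**Working it through.** **The plan's own figure.** The article gives 80% power for the month-3 t-test with 30 per group, a one-point difference and SD 1.35. The noncentrality is 1 / (1.35 × √(2/30)) = 2.87. The noncentral t with 58 degrees of freedom gives 80.5% (two-sided 5%), so the figure reproduces. It uses one visit and does not involve the mixed model. The article gives no figure for the mixed model itself.

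**Inputs.** Visit times come from the article. With "With 30 patients expected in each cohort", n = 60 for changes pooled over procedures. Between-visit correlations are not given, so those below are assumptions. Complete data and equal variances are also assumed.

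**Formulas.** Let ρ_ij be the true correlation between visits i and j, and ρ̄ its average over all pairs.

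- True SE of a change: SD × √(2(1 − ρ_ij)/n).
- SE under the random intercept: SD × √(2(1 − ρ̄)/n).
- Ratio of model SE to true SE: √((1 − ρ̄)/(1 − ρ_ij)). SD and n cancel.
- Actual error of a nominal 5% test: 2 × P(Z > 1.96 × ratio).

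**Worked case.** Take ρ = 0.9^d with d the gap in months, and visits 1/3/6/12. The six gaps are 2, 5, 11, 3, 9 and 6 months, with correlations 0.810, 0.590, 0.314, 0.729, 0.387 and 0.531, so ρ̄ = 0.560.

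- Month 1 vs 12: √(0.440/0.686) = 0.80, error 11.7%.
- Month 1 vs 3: √(0.440/0.190) = 1.52, error 0.3%.

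**Range of assumptions, visits 1/3/6/12:**

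| Assumed correlation | ρ̄ | 1 vs 12: ratio, error | 1 vs 3: ratio, error |
|---|---|---|---|
| Constant 0.5 | 0.500 | 1.00, 5.0% | 1.00, 5.0% |
| Linear in gap, 0.6 at 0 to 0.4 at 12 months | 0.500 | 0.93, 7.0% | 1.07, 3.5% |
| 0.5 × 0.9^d (heavy visit-level noise) | 0.280 | 0.92, 7.0% | 1.10, 3.1% |
| 0.4 + 0.5 × 0.8^d | 0.563 | 0.89, 8.3% | 1.25, 1.4% |
| 0.8^d | 0.327 | 0.86, 9.3% | 1.37, 0.7% |
| 0.9^d | 0.560 | 0.80, 11.7% | 1.52, 0.3% |

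Adding a floor f to a pure decay, f + (1 − f)r^d, changes nothing: 1 − ρ becomes (1 − f)(1 − r^d) for every pair, and the factor cancels.

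**Baseline as a response (visits 0/1/3/6/12).** With 0.8^d to 0.9^d, the ratio for 0 vs 12 months is 0.83 to 0.76 (error 10.4% to 13.4%). Suppose instead that surgery weakens the link to baseline: 0.3 between baseline and any later visit, 0.6 among postoperative visits. Then ρ̄ = (4 × 0.3 + 6 × 0.6)/10 = 0.48. The ratio is √(0.52/0.70) = 0.86 for 0 vs 1 month and √(0.52/0.40) = 1.14 for 1 vs 12 months. The short interval is now anti-conservative and the long one conservative.

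**Loss of power.** Take a month 1-to-3 change that has 80% power with the correct SE. Power under the model is P(Z > 1.96 × ratio − 2.80), which is 55% at ratio 1.37 and 43% at ratio 1.52.

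**Visit-averaged procedure effect.** Over k visits its variance is proportional to (1 + (k − 1)ρ̄)/k, which depends on the correlations only through ρ̄. The SE is therefore the same under both structures. For 0.9^d with five visits, both give 1.35 × √((2/30)(1 + 4 × 0.581)/5) = 0.284.

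**The case against.** The strongest reply is that the article never says the residuals are independent. A mixed model can carry both a patient random effect and a residual covariance, and an article commonly leaves the latter to the full protocol or SAP. This stands in part: a reader should not infer that the text forces equal correlation. But the article does name its device for within-patient correlation, and the ordinary reading of that device is a random intercept. The point concerns the fit of a stated choice, not a missing detail.

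Second, the direction is not a fact. A reader might infer that long-interval standard errors are too small and short-interval ones too large. That needs correlation that decays with time, and the documents give none. Constant correlation produces no error, and a break at surgery can reverse the direction. This stands fully.

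Third, the large figures come from steep decay with correlation close to 1 at short gaps. Appetite is a 0–10 rating of the previous 24 hours, so visit-level noise is likely. The noise and mild-decay rows show that this brings the month 1 vs 12 error down to about 7% to 8%. This also stands.

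Fourth, an error rate of 0.3% might be read as meaning that early changes are almost never detected. It is the false-positive rate when nothing changes. Power falls, but not to near zero.

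Lastly, a reader might carry the error over to the difference in change between procedures. The stated model has no procedure-by-time term, so it contains no such contrast.

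**Conclusion.** The point holds in a conditional and limited form. Under its ordinary reading, the model assumes equal variances and one correlation across unequally spaced visits. If the true correlation varies with interval, the standard errors for change over time are wrong, and the pattern decides the direction.

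Under assumed decay over visits 1/3/6/12, with equal variances, complete data and model-based standard errors, a nominal 5% test of month 1 vs 12 has about 7% to 12% error. Month 1 vs 3 has about 0.3% to 3.5%. These are illustrations, since the documents contain no correlation from which to choose among them.

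The scope is the secondary analyses of change over time. The documents do not support extending the point to the primary month-3 comparison, its 80% power or the visit-averaged procedure effect; none of these changes. The correction is still worth making, because this model is the stated method for the one-year course and the remedy does not depend on knowing the pattern.

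**What to change.** Replace the patient random effect with wording to this effect: within-patient covariance over visits will be unstructured, fitted by REML, with Kenward-Roger degrees of freedom in unweighted analyses. If that does not converge, a time-decaying covariance (heterogeneous spatial power on actual survey day) with robust standard errors will be used. Where inverse probability weights are applied, sandwich standard errors clustered by patient will be used.

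The unstructured form handles decay, a break at surgery and unequal variances alike. Using actual survey day in the fallback also suits the visit windows. A decaying structure would not capture a break at surgery, so the robust standard errors are an essential part of that fallback.

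**Cost.** A few lines of analysis text, with no change to design or data collection. Four visits need 4 × 5/2 = 10 covariance parameters and five need 5 × 6/2 = 15, which is feasible with about 60 patients. The small downside is possible non-convergence for some outcomes, which the fallback covers.

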## Discussion

Despite the increasing incidence of proximal gastric cancer and P/GEJ cancers [20], the optimal treatment strategy for those cancers, including regimens of adjuvant and neoadjuvant therapy and extent of gastrectomy (such as when a transthoracic approach or TG is needed), remains unknown.

The optimal operation for P/GEJ cancers should achieve complete removal of the primary cancer and regional LNs that harbor risks of metastases while maintaining the best possible QoL for the patient. It should also facilitate a quick return to intended oncologic therapy such as adjuvant chemotherapy. In this context, it is unknown whether and the extent to which PG would result in better QoL than TG.

Kunisaki et al. conducted a PGSAS NEXT survey study of gastric cancer patients who underwent TG or PG [21]. This study utilized a questionnaire developed for postgastrectomy patients in Japan (PGSAS-45), which was validated in patients with stage I gastric cancer without receipt of adjuvant or neoadjuvant therapy [22]. PGSAS-45 consists of 45 question items, and 19 subscale “main outcome measures” are calculated on the basis of responses. The PGSAS NEXT study enrolled 1,020 TG patients and 518 PG patients. The PG patients had better scores in several main outcome measures (weight loss, dumping syndrome, necessity for additional meals, ability to work, dissatisfaction with working, and dissatisfaction with daily life subscales; all *p* < 0.05) and a trend towards a better score in the reflux subscale. This study included a large number of patients, and the results supported the use of PG. However, the following limitations made interpretation of the study results difficult: unbalanced disease stage (more advanced tumors underwent TG and extended LN dissection) and surgical approach (more patients in TG underwent open approach) between groups, reconstruction methods after PG not standardized, and cross-sectional study design, which meant that the survey was sent at various times after surgery.

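### The secondary longitudinal mixed model, as written, gives one visit-averaged procedure difference and cannot show whether recovery differs between MIPG and MITG; it also adjusts for adjuvant therapy, which follows surgery

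*Protocol article*

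**What the plan says.** All model terms come from the Statistical methods section of the protocol article.

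- Purpose: "A linear mixed effects model will be fit to assess the change in QoL over time while accounting for potential intra-patient correlations".
- Structure: time "points will be included as a fixed effect, and" patient as a random effect.
- Other terms: "The surgical procedure received and use of adjuvant or neoadjuvant therapy will be included as covariates".
- Reach: "Similar analyses will be performed to assess the changes in body weight, body mass index, and albumin and hemoglobin levels over time".
- Weights: for the regressions that assess the procedure effect, "the inverse probability treatment weights using propensity scores will be applied as appropriate in addition to any standard statistical methods".

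The Outcome measures section has the questionnaire collected before surgery as well as after it: "scores will also be reported at baseline (preoperative) and 1, 3, 6, and 12 months after surgery". The text does not say whether the pre-operative score is a response in the mixed model or a covariate.

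Two other analyses bear on the point. The sentence before the model plans cohort comparisons of questionnaire items, overall scores, weight, body mass index and "albumin and hemoglobin levels at 1, 3, 6, and 12 months after surgery in the cohorts". The primary analysis, appetite at 3 months, uses propensity-score weights and does not go through the mixed model.

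**The concern.** A model with additive time and procedure terms has a single procedure parameter. It allows the two groups to differ in level but not in the shape of recovery. The study is about short-term benefit and follows patients for 12 months, so whether a difference appears early, fades, persists or reverses is a natural question for its longitudinal analysis. This model cannot answer it, and the same form is carried over to weight, body mass index, albumin and hemoglobin.

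The second issue is the covariate list. Neoadjuvant therapy precedes surgery and is a legitimate adjustment. Adjuvant therapy follows surgery. The Discussion says of the optimal operation: "It should also facilitate a quick return to intended oncologic therapy such as adjuvant chemotherapy". On that reasoning, adjuvant treatment could partly be a consequence of the procedure. Conditioning on it then changes what the procedure coefficient means.

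**Working it through.** **1. The plan's own figure.** Inputs from Statistical methods: 30 per cohort, difference 1 point, SD 1.35, 5% level (two-sided assumed). The standardised difference is 1/1.35 = 0.741, and the noncentral t gives 80.5% power, so the stated 80% reproduces. For attrition, 60/0.95 = 63.2, rounded up to 64, which also agrees. These figures concern the 3-month t-test, not the mixed model.

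**2. What the procedure coefficient estimates.** With balanced data, a random patient intercept and additive terms, the procedure coefficient is the plain mean of the visit-specific differences. The protocol gives no trajectory, so the patterns below are assumptions. They are expressed as size of benefit, because 0 is the best appetite score, and the difference at baseline is taken as 0.

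| Differences at 1, 3, 6, 12 months | Post-operative visits only | Baseline also a response |
|---|---|---|
| 1, 1, 1, 1 | 4/4 = 1.00 | 4/5 = 0.80 |
| 1, 1, 0.5, 0 | 2.5/4 = 0.625 (0.63) | 2.5/5 = 0.50 |
| 1.5, 1, 0.5, 0 | 3/4 = 0.75 | 3/5 = 0.60 |
| 0, 1, 1, 0 | 2/4 = 0.50 | 2/5 = 0.40 |
| -0.5, 1, 0.5, -1 | 0/4 = 0 | 0/5 = 0 |

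In the last four rows the 3-month difference is 1.0. The coefficient falls below it because it averages unequal visits. In the first row it falls only when baseline is a response.

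**3. What that means for detection.** Assume SD 1.35 at every visit, 30 per group, within-patient correlation ρ from 0.3 to 0.7, no dropout and no weights. With m visits:

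- SE of the coefficient = 1.35 × √[(1 + (m − 1)ρ)/m] × √(2/30). For m = 4 this is 0.240 at ρ = 0.3 and 0.307 at ρ = 0.7.
- Noncentrality of the procedure-by-time test = Σ(difference − mean)² / [1.35² × (1 − ρ) × 2/30], on m − 1 and 58(m − 1) degrees of freedom.

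Power with post-operative visits only:

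| Pattern | Main effect, ρ = 0.3 to 0.7 | Procedure-by-time, ρ = 0.3 to 0.7 |
|---|---|---|
| 1, 1, 1, 1 | 99% to 90% | 5% (no interaction exists) |
| 1, 1, 0.5, 0 | 74% to 53% | 65% to 96% |
| 0, 1, 1, 0 | 55% to 37% | 82% to over 99% |
| -0.5, 1, 0.5, -1 | 5% | over 99% |

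Neither test is better throughout. The main effect is the stronger one for a constant difference and is blind to a crossing pattern. For the gently fading pattern the order depends on ρ. The procedure-by-time term makes the visit-specific differences estimable within the model, whichever pattern is true.

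**4. Adjuvant therapy.** Let the total effect on the appetite score be −1 (lower is better). Let adjuvant therapy worsen the score by b points, and let MIPG change the proportion receiving it by Δp. The adjusted effect is then −1 − b × Δp. All three inputs are assumed; take b from 0.5 to 1.5 and Δp from −0.2 to +0.2.

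- b = 1.5, Δp = −0.2: −1 + 0.30 = −0.70.
- b = 1.5, Δp = +0.2: −1 − 0.30 = −1.30.
- Δp = 0: −1.00, no change.

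The adjustment can shrink the effect, enlarge it or leave it alone, and the protocol gives no figure that settles which.

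**The case against.** There are four fair counter-arguments.

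- **Purpose.** The model's stated aim is change in quality of life over time, not a between-group difference in that change, and a time effect adjusted for procedure meets that aim. This stands as a reading of one sentence. However, the same section introduces the regressions that follow as ones that assess the procedure effect, and for that use the single averaged coefficient is limiting.
- **Other analyses cover the visits.** Cohort comparisons at each post-operative visit are planned, and the primary result does not use this model. This stands, and it confines the point to a secondary analysis. Those comparisons do not test whether the trajectories differ, and the text ties no adjusted model to them.
- **Condensed article.** No formula is printed and an interaction is not ruled out; an analysis plan not shown could add one. That tempers confidence. Still, the article does set out the model's terms, and procedure appears only among the covariates.
- **Adjuvant use may stand in for stage.** In a non-randomised cohort the adjustment may remove some confounding. The Discussion sentence on adjuvant chemotherapy is a general aim for the optimal operation and does not say that MIPG and MITG differ in adjuvant use. Both remarks stand.

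A reader might infer that the model generally dilutes the procedure effect, or that adjusting for adjuvant therapy removes part of it. The documents support neither. Dilution requires baseline as a response or a difference that varies over visits, and the text fixes neither. The direction of the adjuvant adjustment is open. A reader might also infer that the study as a whole could miss an early benefit; the 3-month primary analysis and the per-visit comparisons argue against that.

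**Conclusion.** The point holds for the secondary mixed model. As its terms are written, it forces parallel MIPG and MITG curves and returns one visit-averaged difference, so it cannot show differing recovery.

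The size depends on inputs the protocol does not give. The coefficient is 0.63 against 1.0 at 3 months for an assumed pattern of 1, 1, 0.5, 0, and 0.80 for a constant 1-point difference if baseline is a response. It is the full 1.00 for a constant difference over post-operative visits only. These values assume balanced data, no weights, a random intercept and no baseline difference.

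Because adjuvant therapy is in the model, the coefficient may not be the total procedure effect. Under the assumed inputs it ranges from −0.70 to −1.30 around a true −1, with the sign of the distortion unknown and possible confounding by stage on the other side.

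**What to change.** In Statistical methods, respecify the longitudinal model as follows.

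- **Responses:** the 1, 3, 6 and 12 month visits, with time as a categorical factor.
- **Fixed effects:** procedure, procedure-by-time and the baseline score as a covariate. The alternative is to keep baseline as a response with the groups constrained equal there; in a non-randomised cohort that constraint is credible only after weighting or adjustment.
- **Reporting:** the procedure difference at each visit with a 95% CI, plus the procedure-by-time test.
- **Adjustment:** keep neoadjuvant therapy, and preferably add pre-operative stage. Leave adjuvant therapy to the sensitivity analyses, where the same section already lists it.

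Apply the same form to weight, body mass index, albumin and hemoglobin.

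The cost is a sentence or two of text and 3 degrees of freedom for the interaction (four visits minus one). No new data are needed: baseline scores are already scheduled, and pre-operative imaging findings are among the items listed for collection from the medical record where available.
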